## Methods/Design

### Protocol overview

The Prodige 22 - ECKINOXE trial is a multicenter randomized phase II trial designed to evaluate efficacy (response rate) and feasibility (safety, tolerability) of two chemotherapy regimens (FOLFOX-4 alone and FOLFOX-4 + Cetuximab) in a peri-operative setting in patients with stage II/III CC. Control arm includes patients for whom standard treatment comprises surgery followed by adjuvant FOLFOX-4 chemotherapy. This phase II study will assess the feasibility of a peri-operative strategy in these patients and the impact of adding cetuximab in this setting for patients with *RAS* wild type tumors.

A double central, independent and blinded review of imaging and pathology is planned. All eligible patients will be randomized to either surgery alone or neoadjuvant chemotherapy with simplified FOLFOX-4. Patients randomized to the simplified FOLFOX-4 arm will be randomized to receive Cetuximab or not if they are *RAS* WT

Thus based on the *RAS* status of the primary tumor the design will be: Arm A vs. Arm B vs. Arm C for *RAS* WT patients and Arm A vs. Arm C for those *RAS* mutated (Fig. 1)

Arm A: simplified FOLFOX-4 alone every 2 weeks for 4 cycles, followed by colectomy, followed by simplified FOLFOX-4 alone every 2 weeks for 8 cycles.

Arm B: Cetuximab plus simplified FOLFOX-4 every 2 weeks for 4 cycles, followed by colectomy, followed by Cetuximab plus simplified FOLFOX-4 every 2 weeks for 8 cycles.

Arm C (control arm): Colectomy followed by simplified FOLFOX-4 alone every 2 weeks for 12 cycles. Adjuvant chemotherapy will be given to all patients with stage III CC and according to the local practices for stage II cancer.

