**Fig. 2 Fig2:**
[figure not shown]
The Tumor Regression Grade (TRG), as simplified to three categories by Ryan (19). TRG1: Major response; TRG2: Intermediate response; TRG3: No response

Secondary endpoints are the following: (i) postoperative morbidity (occurring within 60 postoperative days) graded 0 to 5 according to the Clavien-Dindo classification [20]. If grade 3 or 4 complications occur at a rate ≥ 10 % in either neoadjuvant chemotherapy arm, the arm will be declared hazardous (see section statistical analysis); (ii) the safety of neoadjuvant therapy will be assessed by the systematic collection of toxicity data related to chemotherapy, the total number of cycles administered pre-operatively (documenting reasons for early termination), and the systematic collection of GI symptoms. In addition, complications related to the in situ tumor that could delay the date of surgery or require emergency colonic surgery or stenting, will be documented. These parameters will be evaluated after administration of the first cycle of neoadjuvant chemotherapy; (iii) Regression-free survival at 3-years defined as the time interval between the date of randomization and the date of first recurrence (local, regional or metastatic) or date of death (all causes) if no recurrence; (iv) Disease-free survival at 3 years defined as the time interval between the date of randomization and the date of first recurrence (local, regional or metastatic), or second cancer, or the date of death without recurrence (all causes) and date of second cancer; (iv) Quality of life (evaluated using the EORTC quality of life (QoL) QLQ-C30 and QLQ-CR29); Quality of life will be assessed at the inclusion, after neoadjuvant chemotherapy, at 1 month after surgery and every 6 months thereafter. The QLQ-C30 consists of 30 items with both multi-items scales and single item measures. The internal validation of QLQ-C30 allowed to identify 15 scales and to generate 15 scores: 5 scores of functional scale (physical functioning, role functioning, cognitive functioning, emotional functioning, social functioning), a global health status scare, a financial difficulties scale and 8 symptoms scale (fatigue, nausea/ vomiting, pain, dyspnoea, insomnia, appetite loss, constipation, diarrhoea). These scores vary from 0 (worse) to 100 (better) for functional and global health scale and from 0 (better) to 100 (worse) for symptoms scales. Targeted QoL dimensions for this trial are Global Health, physical and emotional functioning, fatigue and pain of QLQ-30 as well as dimensions of CR29. A 5 points difference in QoL is considered as minimal clinically important difference (MCID). Time to QoL deterioration will be defined as time interval between randomization and first decrease in QoL score greater or equal to 5 points. Patients without QoL decrease greater or equal to 5 points will be censored at the last follow-up. (v) Quality and completeness of the surgical excision evaluated on pathological criteria (number of lymph nodes examined, the completeness of removed mesocolon, surgical margins); (vi) radiological staging and radiological response. The initial radiological staging based on abdominopelvic CT scan will be compared with the histopathological pTNM staging in the control group. CT scan images will be interpreted by the individual study centers, and reviewed by 2 of the 3 members of our Central Review Committee of Radiology. This dual independent reading will assess inter-observer reproducibility of the radiological response to treatment with a test of concordance. The radiological response will be defined by RECIST (v1.1) [21] on CT scan and evaluated in the neoadjuvant chemotherapy arms. These criteria will be applied to the primary colon tumors (largest diameter) and lymph nodes (smallest diameter). The sum of the diameters of the target lesions will be determined on the pretreatment CT scan (initial staging) and compared with the sum of these measures on the reevaluation CT scan (performed within 3 weeks after the completion of neoadjuvant chemotherapy). Interpretation of the reevaluation CT scan will be centralized and carried out independently by 2 of the 3 members of our Central Review Committee of Radiologists blinded to the pretreatment CT scan staging. This dual independent reading will assess inter-observer reproducibility of RECIST criteria applied to CC, and determine if there is a difference in radiological response between the two chemotherapy regimens under investigation in the study; (vii) Correlation between histopathological and radiological response. The radiological response of the primary tumor as defined by RECIST v1.1 criteria (taken for target lesion, only the primary tumor) will be compared with the histopathological response as defined by TRG-Ryan. Evaluation of this correlation will be centralized and carried out by the Central Review Committee of Radiology and Pathology; (viii) The 5-point regression grading system [22] adapted to CC by our team in a pilot study [15], will also be evaluated in this trial. This assessment will be centralized and carried out independently and blindly (without knowing the treatment arms) by 2 of the 3 members of our Central Review Committee of Pathology. This assessment will determine the inter-observer reproducibility of this grading system in CC after chemotherapy and to assess the specificity of histological "regression" criteria using this grading system. Comparison of the reproducibility (test of concordance) of the two systems of grading regression (TRG-Ryan and TRG-Mandard) will identify the most appropriate system for assessing response to chemotherapy in CC.

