### Treatment methods

The treatment protocols are standardized with regard to radiological and pathological parameters, based on the recommendations of I’INCa, the FFCD, the French Society of Pathology, the French Society of Digestive Endoscopy and the French Society of Digestive Surgery. Treatment application depends on the *RAS* status of the primary tumor (Fig. 1) and must start within 14 days after the randomisation.

Neoadjuvant chemotherapy requires an implantable subcutaneous venous access and will be administrated for 4 cycles. The following assessments will be performed prior to each cycle (every two weeks) before chemotherapy administration: documentation of concomitant medication and concurrent procedures; physical examination; vital signs and ECOG performance status; blood sampling for hematology and clinical biochemistry and recording of adverse events since last cycle (including primary tumor related symptoms or complications). The end of treatment visit must be performed 15 days after the 4^th^ cycle administration.

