#### FOLFOX-4 + Cetuximab chemotherapy

Patients in Arm B only will receive Cetuximab according the same schedule of the FOLFOX chemotherapy, i.e. once every two weeks (on d1, d14, d28, etc.…). Cetuximab will always be administered first, i.e. the Cetuximab infusion should be completed one hour before chemotherapy begins. The Cetuximab dose must always be based on the body surface area (BSA). There is no restriction for Cetuximab in patient with a BSA > 2.0 m^2^. The dosage and administration procedure for Cetuximab is as follows:

- The first infusion is 500 mg/m^2^. As prophylaxis to reduce the risk of an allergic/hypersensitivity reaction, it is mandatory to pretreat the patient as specified below. Cetuximab is administered as follows: the volume is administered over 120 minutes (maximum rate of 5 mL/min). Saline solution (0.9 %) is used to flush the line at the end of the infusion. Vital signs are checked before, during, immediately after and 1 hour after the end of the infusion.

The subsequent weekly doses are 500 mg/m^2^. Cetuximab is administered as follows: the volume is administered over 60 minutes (maximum rate of 10 mL/min). Saline solution (0.9 %) is used to flush the line at the end of the infusion.

Surgery will be performed 3 to 5 weeks after the last cycle of neoadjuvant chemotherapy (in arms A and B) or within 14 days after the randomisation. The anesthetic evaluation, patient’s information regarding the operative procedure and the organization of the hospitalization will be performed according to the local practices of each investigator center. The colectomy will be performed by laparotomy or laparoscopy (investigator discretion) with respect of the oncological quality criteria of resection. Per and postoperative data will be collected and reported in specific forms.

Adjuvant chemotherapy will be administrated for all patients included in arms A (FOLFOX-4) and B (FOLFOX-4 + Cetuximab). Eight additional cycles will be administrated (for a total of 12 cycles) according the same regimen. In Arm C (control Arm), only patients with stage III CC (on pathological examination) will receive 12 cycles of adjuvant chemotherapy. For those with stage II CC, the decision of adjuvant chemotherapy in this arm will be will be done according to the investigator's discretion.

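### For arm A or B versus arm C, milestone-based quality-of-life visits feed a clock that starts at randomisation, so early deterioration and medians shift even with no true difference

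*Protocol article*

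**What the plan says.** The quality-of-life item among the secondary endpoints (Endpoints section) sets the calendar: "Quality of life will be assessed at the inclusion, after neoadjuvant chemotherapy, at 1 month after surgery and every 6 months thereafter". It then defines the endpoint: "Time to QoL deterioration will be defined as time interval between randomization and first decrease in QoL score greater or equal to 5 points". On censoring it says: "Patients without QoL decrease greater or equal to 5 points will be censored at the last follow-up".

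The treatment sequence differs by arm (Protocol overview). Arm A is "simplified FOLFOX-4 alone every 2 weeks for 4 cycles, followed by colectomy", and arm B follows the same sequence with cetuximab added. Arm C is "Colectomy followed by simplified FOLFOX-4 alone every 2 weeks for 12 cycles".

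The timings stand in the treatment sections. Treatment "must start within 14 days after the randomisation". For the neoadjuvant block, "The end of treatment visit must be performed 15 days after the 4" (that is, after the fourth cycle). Then: "Surgery will be performed 3 to 5 weeks after the last cycle of neoadjuvant chemotherapy (in arms A and B"); the alternative in the same sentence, surgery within 14 days of randomisation, applies to arm C.

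The article gives no assessment in arm C that matches the post-neoadjuvant one.

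**The concern.** The endpoint is a time since randomisation, but the dates on which an event can be recorded are set by treatment milestones, and one of those milestones does not exist in arm C. Both the number and the dates of the looks therefore depend on the randomised arm. A first fall of 5 points can be seen only when a questionnaire is completed, so two groups with the same underlying course can produce different curves.

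What is at stake is the reading of A or B against C on a secondary endpoint, in a trial whose stated aims include feasibility and tolerability of the peri-operative strategy. The primary endpoint is untouched. A and B share one calendar, so the A versus B contrast is also untouched.

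This is not a detail that an unseen analysis plan would settle. The article states both the schedule and the definition, and no later analysis can recover a questionnaire that arm C never received.

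**Working it through.** The documents give no event rate, effect size or power for quality of life, so there is no figure of the plan's to reproduce. The check rebuilds the calendar and then asks what it does when the arms do not differ.

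**Calendar, in weeks from randomisation** (1 month = 4.35 weeks, 6 months = 26.1). Two readings are assumed: the post-neoadjuvant questionnaire is taken at the end-of-treatment visit, and the 6-monthly ones are counted from the 1-month post-operative one.

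- Arm C: surgery at 0-2; first look at 0-2 + 4.35 = 4.3-6.3; next at + 26.1 = 30.4-32.4.
- Arms A/B: start at 0-2; cycle 4 begins 6 weeks after start; the visit 15 days later is at about 8-10.
- Arms A/B surgery: 6 + (3 to 5) + (0 to 2) = 9-13 if counted from day 1 of cycle 4, or 11-15 if counted from the end of that cycle.
- Arms A/B post-operative look: 13.3-17.3 or 15.3-19.3; next at about 39-45.
- Looks, A/B versus C: 2 v 1 by week 26, 3 v 2 by one year, 7 v 6 by three years.

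Every arm has a 26-week gap after its post-operative look. In C it covers about weeks 6 to 30. In A/B it starts about 9 to 13 weeks later for the same starting delay.

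**(a) Identical constant hazard.** Simulation: 1,000 runs, 33 per arm, three-year horizon, two-sided log-rank at 5%. The true medians are assumptions.

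| True median, all arms | Detected by week 26, A/B v C | Observed median (weeks), A/B v C |
|---|---|---|
| 3 months | 57% v 25% | 15.7 v 31.4 |
| 6 months | 33% v 14% | 41.4 v 32.1 |
| 12 months | 19% v 7% | 67.6 v 58.3 |
| 24 months | 10% v 3% | 119.7 v 110.4 |

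A closed form agrees. The share seen by week 26 is 1 - 2^(-t/m), where t is the last look before week 26 and m the true median. With t at the mid-points 15.3 (A/B) and 5.3 (C) and m = 26.1, this gives 33% and 13%.

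The early share is always higher in A/B. The median is earlier in A/B at a true median of 3 months and later in A/B at 6 months or more. Log-rank rejection is about 5-8% and the hazard ratio 0.94-1.03 (33 or 66 per arm).

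**(b) Identical chance p of a 5-point fall at each look, looks independent.** By week 26 this is 1 - (1-p)^2 against p: 36% v 20% (p = 0.2), 51% v 30% (0.3), 64% v 40% (0.4), 75% v 50% (0.5). Over three years it is 1 - (1-p)^7 against 1 - (1-p)^6: 79% v 74% (p = 0.2) and 92% v 88% (p = 0.3). Log-rank rejection is about 7-10%, with hazard ratios up to 1.12.

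**(c) The same post-operative dip in every arm.** With 70% deteriorated one month after surgery, 30% after neoadjuvant chemotherapy and 20% at later looks, the medians are 15.3 v 5.9 weeks, the hazard ratio is about 0.68 and rejection is 32% (33 per arm) to 54% (66 per arm). Ignoring the extra A/B look raises rejection to 52-75%. The difference here therefore does not come from the extra look. It comes from the dip occurring later in A/B. With a 50% dip instead, rejection is 7-11%.

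**The case against.** Tying questionnaires to milestones is a defensible choice, because it measures recovery at the same point after surgery in every arm. That stands, and it is why the 1-month post-operative questionnaire should stay.

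A reader might infer from the calendar that the later post-operative look in A/B is itself a measurement bias. The documents do not support this. The questionnaire follows surgery by one month in every arm; what differs is the date of surgery. Most of that lag is real deferral of the operation, and the rejection rates in scenario (c) are not false-positive rates.

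A reader might also infer that the whole endpoint is driven by visit dates and cannot be interpreted. That goes too far. Without a marked post-operative dip, log-rank error stays at about 5-10%, and over three years the imbalance is one look in seven. The contrast in scenario (b) is largest early on. It also assumes independent looks: changes from a shared baseline are correlated, which reduces the gain from a second look without removing it.

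Finally, the article specifies no between-arm test of quality of life, and the choice of survival or longitudinal model can be left to an analysis plan. Both are true. Neither supplies the missing arm C assessment.

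**Conclusion.** The point holds for A or B versus C only. One additional early look and different dates shift the observed medians and the share with early deterioration when nothing differs between arms. The early share is roughly doubled or more under a constant hazard (for example 33% v 14%). The direction of the median shift depends on a rate the documents do not give. The formal test is only mildly affected.

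The calendar rests on the two readings named above; other readings move dates by weeks but leave the asymmetry. All deterioration rates are assumptions.

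The Randomisation section places randomisation four to eight weeks after surgery. This conflicts with the Protocol overview and the treatment sections, in which surgery follows randomisation. The calendar uses the latter, and the passages must be reconciled, since every date here depends on them.

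This is a worthwhile correction to a secondary endpoint.

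**What to change.** - Keep the 1-month post-operative questionnaire in all arms.
- Add one arm C questionnaire at about week 8-10 from randomisation, matching the A/B post-neoadjuvant visit.
- Count the 6-monthly questionnaires from randomisation in all arms. Each arm then has two early looks followed by common dates. The two early dates still differ partly, because surgery does.
- Analyse time to deterioration for A/B versus C as interval-censored, or compare scores with a longitudinal model at the common times. Do not simply drop the A/B pre-operative look.
- Reconcile the stated timing of randomisation relative to surgery.

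Cost: one extra questionnaire in arm C. Counting from randomisation otherwise moves dates, and brings at most one more form (month 36) inside the three years. No extra procedure is needed.

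No corrected figure can be given, because the documents state no quality-of-life rates.

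### Time to QoL deterioration counts a fall of at least 5 points as the event, but on the targeted fatigue and pain scales a fall is an improvement

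*Protocol article*

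**What the plan says.** All the relevant text is in the Protocol article, Endpoints, in the secondary endpoint on quality of life (QLQ-C30 and QLQ-CR29).

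- **Direction of functional and global scores:** "These scores vary from 0 (worse) to 100 (better) for functional and global health scale".
- **Direction of symptom scores:** "from 0 (better) to 100 (worse) for symptoms scales".
- **Which scales are symptom scales:** "8 symptoms scale (fatigue, nausea/ vomiting, pain, dyspnoea, insomnia, appetite loss, constipation, diarrhoea".
- **Targets:** "Targeted QoL dimensions for this trial are Global Health, physical and emotional functioning, fatigue and pain of QLQ-30", together with the CR29 dimensions.
- **Threshold:** "A 5 points difference in QoL is considered as minimal clinically important difference (MCID"), with no direction attached.
- **Event:** "Time to QoL deterioration will be defined as time interval between randomization and first decrease in QoL score greater or equal to 5 points".
- **Censoring:** "Patients without QoL decrease greater or equal to 5 points will be censored at the last follow-up".

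No other section gives a separate event rule for symptom scales or says that their scores are reversed before analysis.

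**The concern.** The paragraph sets out two opposite scoring directions and then defines deterioration with a single direction, downward. That suits scales on which a high score is good. It does not suit fatigue and pain, where a high score is bad and a fall is what one hopes to see.

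The Protocol overview makes feasibility, including tolerability, a purpose of the trial, and the Discussion makes good tolerance of neoadjuvant chemotherapy a precondition for the strategy. Fatigue and pain are the only two QLQ-C30 symptom scales among the targets. If the written rule were programmed, the curves for these two scales would carry the label of deterioration but show time to improvement. An analyst who coded them sensibly would depart from the published definition and would have to explain that departure.

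**Working it through.** The plan states no figure that depends on this definition, so there is nothing to reproduce. The check applies the stated rule to each targeted QLQ-C30 scale.

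**Rule as written.** Event if change = later score − reference score ≤ −5. With no such change, the patient is censored at last follow-up.

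**Scale by scale**, using the directions given in the same paragraph:

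| Targeted scale | High score means | A fall of ≥5 means | Rule counts worsening? |
|---|---|---|---|
| Global health | better | worsening | yes |
| Physical functioning | better | worsening | yes |
| Emotional functioning | better | worsening | yes |
| Fatigue | worse | improvement | no |
| Pain | worse | improvement | no |

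The rule has the wrong direction on 2 of 5 scales: 2 / 5 = 40 %.

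**Illustration.** The scores are assumed and serve only to show the coding.

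1. Global health 67 to 58: 58 − 67 = −9. The patient worsened and an event is counted, which is correct.
2. Fatigue 44 to 33: 33 − 44 = −11. The patient improved, yet a deterioration event is counted.
3. Fatigue 33 to 56: 56 − 33 = +23. The patient worsened, yet no event is counted; if no qualifying fall follows, the patient is censored.
4. Fatigue 33 to 56 to 44: against the first value, 44 − 33 = +11, no event; against the preceding value, 44 − 56 = −12, an event. The definition does not name the reference value. A patient who worsens may therefore still enter as an event, but at the time of partial recovery.

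Case 4 matters because quality of life is measured repeatedly: at inclusion, after neoadjuvant chemotherapy, one month after surgery and then every six months. The written rule is not simply a mirror image of the right one. It measures something else.

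**With a rule for each direction** (change ≤ −5 for the three functional and global scales, change ≥ +5 for fatigue and pain), all 5 of 5 scales count worsening as the event.

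**The case against.** The strongest reply is that the wording is merely loose. The event is called deterioration, both scale directions are set out just before it, the 5-point threshold has no sign, and the censoring sentence speaks of a fall in QoL rather than in a score. An analyst reading the whole paragraph would probably code worsening as the event. The article is also condensed, and a full protocol or analysis plan may give the coding for each scale.

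Part of this stands: a reversed analysis is not the likely outcome. It does not rescue the definition. The event sentence refers to the score and gives a threshold in points, so its plain meaning is a numerical fall. This is a rule stated wrongly for two named targets, not a detail left to another document.

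The other side is right to limit the consequences. Three stronger conclusions are tempting, and the document supports none of them:

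- **Every patient who worsens is censored.** Censoring follows only if no fall of at least 5 points occurs as well.
- **The comparison of arms is reversed.** That is possible but not shown. The article gives no QoL distributions by arm from which it could be derived.
- **The CR29 symptom scores are inverted too.** The article lists no CR29 scales and gives no direction for them.

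Quality of life also enters no stated decision rule. The safety of neoadjuvant treatment has its own secondary endpoints (toxicity, cycles given, GI symptoms, complications of the tumor in situ, postoperative morbidity), and the interim and final decisions rest on TRG1 counts and postoperative morbidity.

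**Conclusion.** The definition is wrong as written for fatigue and pain, 2 of the 5 named QLQ-C30 targets. On these scales an improvement of at least 5 points is a deterioration event, and worsening without such a fall is censored. The analysis would measure time to improvement and could mislead on the comparison of arms. Global health, physical functioning and emotional functioning are correctly handled.

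The conclusion rests on the scale directions printed in the same paragraph and on reading the event sentence literally; it needs no outside source. A reader might infer that the trial's tolerability conclusion would have the wrong sign. The document does not support that, because tolerability is judged mainly on other data and no effect between arms can be computed. The fault is confined to one derived measure of a secondary endpoint. The TRG primary endpoint, the Simon boundaries and the sample size are untouched.

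**What to change.** In the quality-of-life paragraph of Endpoints:

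1. Define deterioration as a decrease of at least 5 points from baseline for global health and the functional scales, and as an increase of at least 5 points from baseline for symptom scales (fatigue and pain among the targets).
2. State the scoring direction of each CR29 dimension and apply the matching rule.
3. Reword the censoring sentence so that patients without deterioration, as defined for that scale, are censored at last follow-up.

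The cost is a few sentences, made before the analysis. No new data are needed, and the 5-point threshold stays as it is.

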### Data collection and follow-up

For all patients, follow-up assessment will be performed until recurrence and/or death. For the study, the recurrence free survival will be assessed at 3 years. For patients included in the present trial, the follow-up will be systematic and performed thereafter this period according to the good clinical practices. The follow-up schedule and investigations proposed for the present study are those recommended by the FFCD [8].

Every 6 months, the following investigations will be performed: tumor assessment, CEA measurement, survival status, additional cancer therapy. Moreover, the following assessments will be performed during the follow-up: colonoscopy 3 years after surgery then every 3 to 6 years, assessment of neurological toxicity, and assessment of electrolytes (magnesium, calcium, potassium) at the second follow up visit (12 months after surgery) if still abnormally decreased at end of treatment assessment.

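### Time to quality-of-life deterioration is censored at last follow-up, not at the last completed questionnaire, so unobserved time counts as deterioration-free

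*Protocol article*

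**What the plan says.** The quality-of-life item in the Endpoints section of the protocol article fixes three things.

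- **Event and time origin:** "Time to QoL deterioration will be defined as time interval between randomization and first decrease in QoL score greater or equal to 5 points".
- **Censoring:** "Patients without QoL decrease greater or equal to 5 points will be censored at the last follow-up".
- **Schedule of forms:** "Quality of life will be assessed at the inclusion, after neoadjuvant chemotherapy, at 1 month after surgery and every 6 months thereafter".

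The section Data collection and follow-up describes what follow-up is. On its length: "For all patients, follow-up assessment will be performed until recurrence and/or death". On its content: "Every 6 months, the following investigations will be performed: tumor assessment, CEA measurement, survival status, additional cancer therapy". The horizon for the survival endpoint is also given there: "For the study, the recurrence free survival will be assessed at 3 years".

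No sentence ties the censoring date to the last QoL form, or says what happens when a patient stops completing forms before clinical follow-up ends.

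**The concern.** The event and the censoring date rest on different sources of information. The event needs a completed QLQ-C30 or QLQ-CR29. The censoring date needs only a follow-up contact, which may be a scan, a CEA result or a note of survival status.

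Take a living, relapse-free patient who completes the forms at inclusion and after neoadjuvant chemotherapy, returns none later and attends clinic to month 36. QoL was observed for about 2 months (4 cycles of 2 weeks), yet the patient contributes 36 deterioration-free months. A patient with only the inclusion form also contributes 36 months, although no change from baseline could ever have been recorded.

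The error has one direction. Deterioration that occurs after the last form is never counted, but the time is, so the deterioration rate is too low. The more forms an arm loses, the better its QoL looks. If completion differs between the cetuximab, FOLFOX and control arms, the comparison is biased towards the arm with the poorer completion. This is separate from how relapse or death is handled, because it concerns patients who are still under clinical follow-up.

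**Working it through.** The article gives no rate, event count or power for this endpoint, so there is no figure to reproduce. What follows illustrates the two censoring rules.

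**Inputs from the document:** event definition, censoring rule, forms every 6 months after the postoperative form, 3-year horizon.

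**Assumptions (not in the document):** forms at 3.3, 9.3, 15.3, 21.3, 27.3 and 33.3 months; clinical follow-up of every patient to month 36; exponential time to deterioration with S(36) = 50 %; a probability d at each form of stopping questionnaires for good, unrelated to QoL.

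**Step 1, true curve.** S(t) = 0.5^(t/36). At the six forms S = 0.938, 0.836, 0.745, 0.664, 0.591 and 0.527. The probability of deteriorating in the interval before form k is D_k = S(k−1) − S(k) = 0.0616, 0.1024, 0.0912, 0.0813, 0.0724 and 0.0645, with sum 0.473. The true deterioration-free proportion at the last form is 52.7 %.

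**Step 2, censoring at last follow-up.** An event in interval k is seen only if form k is completed, which has probability (1−d)^k. Everyone without a recorded event is carried to month 36, so nobody is censored earlier and the Kaplan-Meier estimate is 1 − Σ (1−d)^k D_k. For d = 0.05 the sum is 0.0585 + 0.0924 + 0.0782 + 0.0662 + 0.0560 + 0.0474 = 0.399, which gives 60.1 %.

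**Step 3, censoring at the last completed form.** At form k the events are (1−d)^k D_k and the number at risk is (1−d)^k S(k−1). The dropout factor cancels, the hazard is D_k / S(k−1), and the product over the six forms is 52.7 % for every d.

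**Step 4, person-time.** This is the time to the last completed form (or to the event), divided by the time that the written rule counts.

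| Dropout per form | True | Last follow-up | Excess (points) | Last form | Observed / counted time |
|---|---|---|---|---|---|
| 0 % | 52.7 % | 52.7 % | 0 | 52.7 % | 0.95 |
| 2 % | 52.7 % | 55.8 % | 3.1 | 52.7 % | 0.87 |
| 5 % | 52.7 % | 60.1 % | 7.4 | 52.7 % | 0.77 |
| 10 % | 52.7 % | 66.5 % | 13.8 | 52.7 % | 0.62 |
| 15 % | 52.7 % | 71.9 % | 19.2 | 52.7 % | 0.51 |
| 20 % | 52.7 % | 76.5 % | 23.8 | 52.7 % | 0.42 |

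A simulation of 100,000 patients under the same assumptions agrees: 60.1, 66.6, 71.9 and 76.7 % at 5, 10, 15 and 20 % dropout with last-follow-up censoring, and 52.5 to 53.2 % with last-form censoring. The event count is the same under both rules, so a rate per person-time is understated by 1 − 0.77 = 23 % at 5 % dropout and by 1 − 0.42 = 58 % at 20 %. About 5 % of this is present without any dropout, because the last form precedes month 36.

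**Step 5, two arms with identical QoL.** With 5 % dropout in one arm and 15 % in the other, the written rule shows 71.9 − 60.1 = 11.8 points of difference where none exists.

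**Step 6, other assumptions.** A second simulation (40,000 patients per arm) used a median time to deterioration of 18 months and forms at 3, 4.5, 10.5, 16.5, 22.5, 28.5 and 34.5 months. The true proportion at the last form is 26.5 %. Last-follow-up censoring gives 26.6, 39.0, 50.2 and 59.0 % at 0, 5, 10 and 15 % dropout; last-form censoring gives 26.1 to 26.6 %. With a true hazard ratio of 1, the written rule gives 0.79 for 5 % versus 10 % dropout and 0.62 for 5 % versus 15 %, in favour of the arm with more missing forms. Last-form censoring gives 1.00 in both. With equal dropout both rules give 0.98 to 1.00.

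**The case against.** The strongest counter-argument is the wording. The censoring sentence stands inside the quality-of-life item, directly after the definition of the endpoint, and may have been meant as the last QoL follow-up. Forms are also planned every 6 months, the same interval as the clinic visits, so with full completion the two dates nearly coincide. That reading is possible, but the text does not state it, and the article's own follow-up section uses the word for clinical visits. If it was intended, the remedy is the same sentence.

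Several limits on the size do stand:

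- The document gives no completion rate, deterioration rate or end date for the forms. The percentages above illustrate the mechanism and are not a forecast.
- At 0 % dropout the proportion is unbiased, and at 2 % the excess is about 3 points.
- Forms that are missed and later resumed leave the last form in place and do little harm. The damage comes from patients who stop for good.
- Follow-up runs to recurrence or death, so not every patient reaches month 36.
- The between-arm bias needs unequal completion. The document does not show that. It is plausible, because treatment differs between arms and stage II control patients may receive no adjuvant chemotherapy.
- If patients stop forms because they feel worse, censoring at the last form is biased as well. It still does not record them as known to be well for months in which nobody asked.

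QoL enters no decision rule. The phase III decision rests on TRG1 counts and postoperative complications.

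**Conclusion.** The concern holds. The protocol article states a censoring rule that, as written, credits patients with deterioration-free time during which deterioration could not be observed. Because the rule is stated, this is not a detail left to an analysis plan: a plan that follows it inherits the bias, and one that does not contradicts the protocol.

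Under permanent dropout of 5 to 20 % per form that is unrelated to QoL, with clinical follow-up to 36 months, the deterioration-free proportion is 7 to 24 points too high. At 2 % it is 3 points too high, and with complete questionnaires the proportion is not biased. A false difference between arms arises only if completion differs. The point affects one secondary endpoint and should be corrected; the TRG analysis and the sample size are untouched.

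**What to change.** Replace the censoring sentence with: *Patients without QoL deterioration are censored at the date of their last completed questionnaire with a valid score for that dimension; patients with no questionnaire after baseline are censored at randomisation.* Report questionnaire completion by arm and visit beside the result, so that readers can judge whether dropout could be related to QoL.

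The cost is one sentence and one table. No new data should be needed, since dating the event already requires the questionnaire date. Follow-up time for this endpoint will be shorter than clinical follow-up, which correctly reflects what was observed.
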